#### ***Primary endpoints:***

- Frequency of adverse events during iSIL treatment.
- Kinetics of the decline in HCV-RNA after 2 weeks of iSIL treatment (difference in IU/ml from day 1 to day 15, see flow-chart below).

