### **9.2 Day + 1 (baseline visit), immediately previous to iSIL administration**

- Check for inclusion and exclusion criteria
- Documentation of adverse events
- Concomitant medication
- Physical examination
  - Including blood pressure while sitting (right/left), pulse rate, temperature (degree Celsius), cardiac auscultation, chest auscultation, abdominal auscultation, brief neurological examination

- Safety laboratory: full blood count, electrolytes (sodium, potassium), ASAT, ALAT, total and fractionated bilirubin, gammaGT, total protein, alkaline phosphatase, creatinine, albumin, INR
  - 10ml Heparin blood
- HCV-RNA, HIV-RNA
  - 10ml EDTA blood
- CD3/4/8 count
  - 3ml EDTA blood
- Drug level of current ART
  - 10ml EDTA blood
  - Note the time-point (date, hour, minutes) of the last intake and the dosage (milligram) on the electronic CRF
  - Blood (10 ml) must be collected in EDTA solution vacutainer tubes. The tubes containing EDTA solution should be stored at +4°C. Tubes must be identified with the patient ID number and sample number as soon as blood has been collected
  - Blood samples must be brought to the laboratories without delay (maximum 30 min after blood collection).
  - Treatment of samples: centrifugation at 1500g for 10 min at +4°C. In a class II biohazard hood plasma (obtained after centrifugation) should be divided in three labelled tubes (of approximately 1mL each) ready for freezing at -80 ° C, within one hour after collection. If this deadline cannot be met, please keep the sample at 4° C until centrifugation and freezing
- Silibinin drug-level (Cmin (T0, pre-dose), Cmax (i.e immediately after the end of silibinin infusion) and one sampling at T4 (i.e. 4 hour after the end of silibinin infusion)
  - Blood (6 ml) must be collected in ACD (acid citrate dextrose) solution vacutainer tubes. The tubes containing ACD solution should be stored at +4°C. Tubes must be identified with the patient ID number and sample number as soon as blood has been collected
  - Blood samples must be brought to the laboratories without delay (maximum 30 min after blood collection).
  - Treatment of samples: centrifugation at 1500g for 10 min at +4°C. In a class II biohazard hood plasma (obtained after centrifugation) should be divided in three labelled tubes (of approximately 1mL each) ready for freezing at -80 ° C, within one hour after collection. If this deadline cannot be met, please keep the sample at 4° C until centrifugation and freezing.

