## **10.6 Potential risks/adverse events and treatment**

Due the limited size of the patient population with HCV treated with Legalon® SIL, the estimated incidence of possible adverse reactions provided below is based on the balance between the uncertainty of the actual proportions observed and the low absolute number of patients reporting the reaction, in comparison with the control group in controlled studies and taking into account the supposed relationship with treatment:

- Very common: sensation of heat.
- Common: diarrhoea, bilirubin increased, nausea, vomiting, headache.
- Uncommon: abdominal pain, fever, asthenia, shivering, feeling of body temperature change, abdominal discomfort.
- Rare: somnolence.

It should also be considered that the above incidences are not readily transferable to the general HCV patient population (probably with the exception of sensation of heat, diarrhoea and bilirubin increased), as most of the data on which they are based were derived from studies in special patient subgroups, often in critical conditions, such as patients in liver peri- or post-transplant situations.

Sensation of heat, feeling of body temperature change, shivering and fever usually occur during infusions at the beginning of treatment with Legalon® SIL and recede spontaneously on continuation of therapy. Slow infusions of Legalon® SIL might reduce their occurrence.

Bilirubin increase is a transient effect which spontaneously subsides upon Legalon® SIL discontinuation without treatment. Data collected so far indicate that bilirubin increase following Legalon® SIL administration is not accompanied by cholestatic or hepatotoxic effects.

No contra-indications are known other than hypersensitivity to the active substance or to the excipients. No interactions with other medicine or other forms of interaction are known.

The risk for clinically relevant metabolic drug interactions can be considered low based on in vitro studies and supported by clinical data collected in patients receiving Legalon® SIL and other concomitant medications who did not require any dose adjustments.

There are no adequate data from the use of Legalon® SIL in pregnant women and for this reason Legalon® SIL administration during pregnancy and lactation is not recommended.

There are no reported effects on ability to drive and use machines.  
No case of overdose has been reported.

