## 10.7 Assessment of safety laboratory parameters

The laboratory tests listed in Table below will be performed at the laboratory of each study site and the laboratory of [name] in Lausanne. For time points of laboratory sampling refer to the Flow Chart. Laboratory results of the patients will be available to the investigator of each study site and selected abnormal laboratory alerts will be sent automatically to the sponsor within 24 hours. Clinically relevant laboratory values should be commented on lab report print-outs. A clinically relevant value may be either in- or outside the reference range. Out-of-range data judged as clinically significant (CS) by the Investigator has to be report as an adverse event. Clinically relevant abnormal laboratory test results must be confirmed and should be repeated until normalization or stabilization or until an alternative explanation has been found.

| Category             | Test name                                                                                                                                                                                                                                                                                                               |
|----------------------|-------------------------------------------------------------------------------------------------------------------------------------------------------------------------------------------------------------------------------------------------------------------------------------------------------------------------|
| Haematology          | Hematocrit (Hct)
Hemoglobin (Hb)
Red Blood Cell Count/ Erythrocytes
White Blood Cells / Leukocytes
Platelet Count/ Thrombocytes
Diff. Automatic Neutrophils (relative count)
Eosinophils (relative count)
Basophils (relative count)
Monocytes (relative count)
Lymphocytes (relative count) |
| Coagulation          | Prothrombin time (Quick and INR)                                                                                                                                                                                                                                                                                        |

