## **12 STATISTICS**

### **12.1 Statistical and Analytical Plans**

The analyses of the primary and secondary endpoints of this non-comparative study will be purely descriptive. The average decline of HCV RNA during the lead-in phase (day +1 to day +15) will be expressed in  $\log_{10}$  IU/ml using methods for left-censored data (Tobit regression) (18) in case of undetectable values are encountered and represents the primary efficacy analysis and will be performed in the evaluable patients. We will further report the percentages (with 95% CI) of patients achieving undetectable levels of HCV RNA at the various time points. We will also attempt to analyse factors associated with  $\log_{10}$  HCV RNA response with mixed effects models (19) taking into account all measured HCV values from day -14 to day + 15. In these models, slopes will be allowed to change at day+1 and day +15. Potential co-factors will be first assessed in univariable and bivariable models to detect interactions and collinearities. Relevant effect modifiers and confounders will then be included in multivariable models. The following co-factors will be considered: age, gender, IL28B genotype, BMI, CD4 values and HIV RNA. We will look at the potential co-factors in univariable models first and only include relevant confounding variables in the multivariable analysis. Safety analyses will be performed including all patients that received at least one dose of the study medication (Safety Population). Adverse events will be reported in percentages (with 95% CI) of patients experiencing an event (for clinical events and abnormal laboratory values considered clinically significant by the Investigator – this represent the primary safety analyses) or the percentages below/above 1x and 2x normal range limits for laboratory values.

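### The supportive laboratory table counts values against normal limits without reference to day 1, so it mixes pre-existing with on-treatment abnormality

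*Protocol*

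**What the plan says.** **Section 12.1** puts two different summaries into one sentence whose subject is adverse events.

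- The first is the primary safety analysis: the percentage of patients, with 95% CI, who have an event, "for clinical events and abnormal laboratory values considered clinically significant by the Investigator".
- The second is the laboratory tabulation: "or the percentages below/above 1x and 2x normal range limits for laboratory values". It names no time point, baseline value, change or shift.

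**The Synopsis (Statistical Methodology)** carries a shorter version. There the event percentages are for clinical events only, so the range-limit percentages are the sole laboratory summary.

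**Section 5.1** gives the primary safety endpoint as "Frequency of adverse events during iSIL treatment".

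**Section 9.2** requires blood before the first dose: "Safety laboratory: full blood count, electrolytes (sodium, potassium), ASAT, ALAT, total and fractionated bilirubin, gammaGT" and further tests. The Study Schedule places the safety laboratory at screening and on days 1, 2, 4, 8, 12 and 15.

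**Section 10.2** makes an abnormal test an adverse event only if it comes with symptoms, leads to further work-up or intervention, or changes dosing or participation. **Section 10.7** adds: "Out-of-range data judged as clinically significant (CS) by the Investigator has to be report as an adverse event". It also says: "A clinically relevant value may be either in- or outside the reference range".

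**Section 10.6** lists the known reactions, among them: "Common: diarrhoea, bilirubin increased, nausea, vomiting, headache".

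**The concern.** Patients enter this study because they have chronic HCV with fibrosis (Sections 6.1 and 7.1), and no exclusion criterion in Section 7.2 caps the liver tests. Some liver-related results can be expected outside the normal range before any study drug is given. There is no control arm, so a patient's own day-1 value is the only available comparator. The HCV RNA endpoint uses it (day 1 to day 15, Section 5.1); the laboratory tabulation does not.

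At stake is whether the one laboratory summary that does not depend on an investigator's opinion can say anything about the drug. The other route, investigator-judged clinical significance, operates in an open-label study (Section 8.7). An objective table would be the natural check on that judgement. A table that largely reflects the patients' condition at entry cannot do this.

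**Working it through.** The Protocol states no laboratory rate, precision target or baseline prevalence, so there is no figure of its own to reproduce. The steps below follow the rule as written.

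**1. What the table returns when the drug does nothing.** Inputs: n = 20 (Section 12.4), and an assumed share p of patients above an upper limit on day 1. The documents do not give p, so a range of 30% to 90% is used for illustration, with no within-patient change. The rule as written counts 20 × p. A count of new crossings from day 1 is 0. Intervals are exact (Clopper-Pearson) 95%.

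| Assumed p | Rule as written | 95% CI | New crossings | 95% CI |
|---|---|---|---|---|
| 30% | 20 × 0.3 = 6/20 | 11.9–54.3% | 0/20 | 0–16.8% |
| 50% | 20 × 0.5 = 10/20 | 27.2–72.8% | 0/20 | 0–16.8% |
| 70% | 20 × 0.7 = 14/20 | 45.7–88.1% | 0/20 | 0–16.8% |
| 90% | 20 × 0.9 = 18/20 | 68.3–98.8% | 0/20 | 0–16.8% |

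The rule gives back the baseline prevalence, whatever it is. The counts depend on p; the direction does not.

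**2. What the table misses when a patient worsens.** A patient beyond twice the limit on day 1 is already in the top category and cannot move. Assume 20% of patients worsen (20 × 0.20 = 4) and that 30% to 50% start beyond twice the limit, independently. Then 4 × 0.3 = 1.2 to 4 × 0.5 = 2.0 of the 4 worsening patients never appear as a new crossing of that limit. These shares are also assumptions.

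**3. The lower-limit category.** Let L be the lower and U the upper normal limit. Taken literally, values below 2 × L include every normal value between L and the smaller of U and 2L. Where U is less than 2L, every normal value qualifies. No assumption is needed here.

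**4. Section 12.1 beside Section 10.2.** Section 12.1 reports range crossings as a form of adverse event. Under Section 10.2 being out of range is not enough to make a test result an adverse event, and Section 10.7 requires a judgement of clinical significance. The two therefore count different things, yet adverse-event frequency is a primary endpoint.

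**The case against.** The strongest reply is that this table is not the laboratory safety analysis. Section 12.1 names clinical events plus clinically significant laboratory abnormalities as primary. Section 10.1 counts exacerbation of a pre-existing condition as an adverse event, and Section 10.7 requires significant out-of-range results to be reported. A stable abnormality does not enter the primary count merely by being out of range, and a significant rise above twice the limit does enter it. This stands, and it limits the point to the supportive table. What remains is that the primary route depends on unblinded judgement and that the Synopsis omits it for laboratory values.

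A second reply is that Section 12.1 fixes no time point, so a by-visit table could set day 1 beside later days, and that shift tables are ordinary content for a statistical analysis plan, which is not shown. This stands in part. The Protocol does state a rule, however. A later plan that followed it would inherit the defect, and a by-visit table of percentages would still not show which patients moved.

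Some stronger readings are tempting and should be resisted.

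- A reader might infer that new worsening is hidden from the trial. It is hidden only inside this table.
- A reader might infer that the bilirubin rise expected from Section 10.6 would be masked. That would require bilirubin to be commonly abnormal on day 1, and the documents do not say so; if it starts mostly normal, the table would show the rise.
- A reader might want a standard toxicity scale in place of the one- and two-fold limits. That is a preference, not a correction.

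**Conclusion.** The point holds as a limited weakness in the supportive laboratory tabulation. As written, the table cannot separate abnormality at entry from abnormality on treatment, and it cannot register worsening beyond twice the limit on day 1. The lower-limit category is unworkable if read literally, and placing range crossings among adverse events does not fit Section 10.2.

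The size cannot be fixed from the documents. The range of 6 to 18 of 20 against 0 of 20 is an illustration that rests on an assumed baseline prevalence of 30% to 90% and no within-patient change. The structural conclusions do not depend on it. The primary safety analysis in Section 12.1 is not invalidated. This is best treated as a free improvement.

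**What to change.** In Section 12.1, replace the range-limit clause with the following.

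1. For each laboratory test, report the percentage of patients (95% CI) whose worst value from day 2 to day 15 is in a worse category than their day-1 value, with the shift table.
2. Report change from day 1 as well, notably for total and fractionated bilirubin, ASAT and ALAT. This is needed because a shift table that keeps the same categories still cannot move a patient who starts in the top one.
3. Drop the category below twice a lower limit, or redefine it so that normal values cannot fall into it.
4. Present the laboratory table separately from the adverse-event count.
5. Align the Synopsis with Section 12.1, so that both name clinically significant laboratory abnormalities as part of the primary safety analysis.

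One caution in reading the result: the worst of up to five later values is compared with a single day-1 value, so ordinary variation alone will produce some shifts. The change from screening to day 1, both before dosing, gives a rough gauge of that.

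The cost is analysis wording and programming only. No visit, sample or test is added, because the safety laboratory is already taken at screening and before the first dose.

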score  $\geq 3$ ), an unfavourable interleukin 28 B genotype and a high baseline HCV viral load. The study results confirmed the efficacy of iSIL in a difficult-to treat patient group and underscored that iSIL could be a valuable treatment-option in patients not responding to PR (12). The potential role of iSIL as rescue therapy in patients not responding to previous combined therapy with PR and a HCV-specific PI was demonstrated by Biermer et al., 9 of the 13 responder patients are in the follow-up period: 3 of them achieved SVR24, 2 achieved SVR12, and 4 had a viral relapse (13). Recent reports also show the efficacy of iSIL in patients with HCV-reinfection after liver transplantation. After 14 days treatment of iSIL in a dosage of 20mg/kg all four patients showed normalization of liver enzymes and a significant decline of HCV-RNA with a mean log-reduction of 2.8 (14). Moreno et al. presented their data about the safety and the anti-HCV activity of a rescue therapy with iSIL in cirrhotic HIV-HCV co-infected individuals at the 19th conference on retroviruses and opportunistic infections (CROI) in 2012. They treated 4 individuals with previous partial response (PR) or relapses to PR with iSIL 20mg/kg for at least 14 days. Three patients started iSIL during PR and nitazoxanide (add-on strategy). Overall, therapy with iSIL led to negative HCV-RNA in 3 subjects and values  $<50$  IU/mL in the remaining. The period of mono-therapy with iSIL produced a time-dependent effect: the mean decrease of HCV-RNA was  $-2.5 \log_{10}$  IU/ml after 1 week and  $-4.62 \log_{10}$  IU/ml after 35 days. However, HCV-RNA rebounded in 4 patients after stopping iSIL. There were no significant adverse events related to iSIL and all patients maintained current antiretroviral therapy (ART) with undetectable HIV RNA (15).

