## 6 STUDY DESIGN AND COURSE OF STUDY

### 6.1 General Design

This study is a multicentre, open-label, interventional study including HCV-HIV co-infected individuals with chronic HCV-genotype 1 infection and documented previous null-response (NR) or partial-response (paR) to standard therapy with SOC and progressed liver fibrosis.

The overall study-duration is 15 days. The first part is the once a day administration of iSIL from day 1 to 14. Since the half-life ( $T_{1/2}$ ) of the administrated study-drug is very short (3 hours), the follow-up of the study-subjects is one day (day 15) and the final visit will be on day 15.

Subsequent to THISTLE (at day 15) we have the intention to include the study-subjects in the SHCS trial # 688. The trial # 688 will investigate the occurrence of HCV-resistance to the HCV-PIs during TT. The duration of the # 688 will contain 48 weeks with a follow-up of 24 weeks. Importantly, we plan to review the results from the THISTLE trial with the data from the SHCS # 688.

The estimated time frame is listed below:

- Submission to ethical committee (Zurich as lead ethical committee): November 2012
- Ethical approval: January 2013
- Swissmedic approval: February 2013
- First patient enrolled: April 2013
- Enrolment: April 2013 to December 2013
- Last patient enrolled: End of December 2013

All included patients will receive a lead-in therapy with iSIL in a dosage of 20mg/kg/day for 14 days followed by standard of care TT. As mentioned above, the follow-up period will contain for one day due to short half-life time of the administrated study-drug. Moreover, a prolonged follow-up period outside THISTLE trial is warranted due to the SHCS trial # 688.

The included patients are HCV-HIV co-infected SHCS participants with chronic HCV-genotype 1 infection and documented previous null-response (NR) or partial-response (paR) to standard therapy with SOC and in urgent need of treatment (i.e. METAVIR fibrosis score  $\geq 2$  or ISHAK fibrosis score  $\geq 4$  or fibroscan stiffness  $\geq 9.5$  kPa). As cut-offs for the fibroscan we used the ones proposed in a recent review by Castera et al (17). NR is defined as less than 2 log10 IU/ml decrease in HCV RNA level from baseline at 12 weeks. paR is defined as more than 2 log10 IU/ml decrease in HCV-RNA level from baseline at 12 weeks of therapy but detectable HCV-RNA at weeks 12 and 24.

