### **12.4 Determination of Sample Size**

In concordance to common safety- or PK-studies a number of 20 enrolled study-subjects should be adequate to make a clear statement regarding safety-issues. During the short lead-in course of 14-days iSIL treatment we expect no significant confounders which significantly influence the primary and secondary outcomes. Because the preliminary data show such a strong effect of iSIL regarding the HCV-RNA decline from

baseline, we expect to demonstrate a clear efficacy of iSIL with a sample size of 20 subjects.

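### The secondary laboratory summary in Section 12.1 counts values beyond 1x and 2x normal limits without reference to day 1, so abnormality present at entry is counted as a safety result

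*Protocol*

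**What the plan says.** Section 12.1 has two layers of safety reporting in one sentence. The first is named as the primary safety analysis: "Adverse events will be reported in percentages (with 95% CI) of patients experiencing an event", covering clinical events and "abnormal laboratory values considered clinically significant by the Investigator". The second, joined by an 'or', is "or the percentages below/above 1x and 2x normal range limits for laboratory values". The synopsis (Statistical Methodology) gives the same 1x/2x rule. Neither place mentions day 1, change, shift or treatment emergence. Neither says whether the percentages are of patients or of values, or whether they are per visit or cumulative.

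The safety analyses include everyone who received at least one dose. Section 6.1 describes the population as genotype 1 patients with previous null or partial response "to standard therapy with SOC and progressed liver fibrosis". Section 7.2 sets no limit on transaminases, bilirubin or any other liver test. Sections 9.1 and 9.2 collect the safety laboratory at screening and again on day 1, immediately before the first infusion. The study schedule repeats it on days 2, 4, 8, 12 and 15.

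**The concern.** A percentage beyond a fixed normal limit describes the state of the patients, not what happened to them on treatment. In a controlled trial a comparator would absorb the background rate. Here there is no comparator, so each patient's own pre-dose value is the natural numerical reference for a laboratory table, and the rule as written does not use it.

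The protocol itself gives grounds for expecting movement in both directions. Section 4.4 reports a series in which "all four patients showed normalization of liver enzymes" on silibinin, which implies raised enzymes at the start. Section 10.6 lists increased bilirubin as a common reaction. The table should be able to separate a new rise from a long-standing one and from an improvement. Frequency of adverse events is a primary endpoint, and this is the only laboratory summary in the protocol that does not depend on investigator judgement, so its ability to show a signal matters even though it ranks second.

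**Working it through.** **Inputs.** N = 20 (Section 12.4) and the 95% confidence level (Section 12.1) come from the protocol. The share of patients out of range on day 1 is not given anywhere, so it is an assumption, varied from 30% to 90%. There is no stated figure to reproduce: Section 12.4 says only that "a number of 20 enrolled study-subjects should be adequate to make a clear statement regarding safety-issues", with no event rate or precision, and Section 12.2 marks hypotheses as not applicable.

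**Formula.** Exact (Clopper-Pearson) limits for x of n: lower = 2.5% quantile of Beta(x, n-x+1); upper = 97.5% quantile of Beta(x+1, n-x). For x = 0 the lower limit is 0 and the upper limit is 1 - 0.025^(1/n).

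**Step 1: no drug effect.** Everyone stays in the day-1 category. The rule counts the 20 x p patients who were abnormal at entry. A treatment-emergent count is 0 among the 20 - 20p patients who were within the limit on day 1.

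| Assumed share abnormal on day 1 | Rule as written (95% CI) | New crossings among those at risk (upper 95% limit) |
|---|---|---|
| 30% | 6/20 = 30% (11.9-54.3%) | 0/14 (23.2%) |
| 50% | 10/20 = 50% (27.2-72.8%) | 0/10 (30.8%) |
| 70% | 14/20 = 70% (45.7-88.1%) | 0/6 (45.9%) |
| 90% | 18/20 = 90% (68.3-98.8%) | 0/2 (84.2%) |

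Check of one upper limit: 1 - 0.025^(1/10) = 30.8%.

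**Step 2: percentages read by visit, with movement both ways.** Day-15 count = day-1 count - normalised + newly crossed. The numbers moving are illustrative.

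| Abnormal on day 1 | Normalise | Newly cross | Day 15 | New crossings among those at risk (95% CI) |
|---|---|---|---|---|
| 10 | 3 | 3 | 10/20 | 3/10 = 30.0% (6.7-65.2%) |
| 12 | 4 | 4 | 12/20 | 4/8 = 50.0% (15.7-84.3%) |
| 14 | 6 | 4 | 12/20 | 4/6 = 66.7% (22.3-95.7%) |

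In the first two rows the visit percentage does not move. In the third it falls from 14/20 to 12/20 while four patients newly cross the limit.

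**Step 3: percentages read cumulatively.** If a patient counts once any value is beyond the limit, day 1 included, the first row of Step 2 gives 10 + 3 = 13/20. Nothing cancels, but 10 of the 13 were abnormal before the first dose.

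**Result.** Entry abnormality is counted on either reading. Offsetting arises only on the by-visit reading.

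**The case against.** - **The table is not the primary safety analysis.** This is correct. Section 12.1 gives that role to clinical events and investigator-judged laboratory values, and an investigator can take day 1 into account. It limits the consequence but does not repair the table.
- **Layout belongs in a statistical analysis plan, which may exist but is not shown.** Partly right. Section 12.1 does not forbid a day-1 comparison, and a plan could add one. But the protocol does state the statistic, in two places, and as stated it has no baseline reference.
- **A by-visit display with a day-1 column would show the pre-treatment percentage.** True, and a reader could then see the background rate. Only the marginal percentages would be visible, however, so the offsetting in Step 2 would remain hidden. The 2x row would reveal worsening only if the new rises exceeded that limit. A reader might infer that both harms occur together in full, but the text fixes neither unit nor time frame. Nor does it say that every value is counted.
- **The size is assumed and the cited series is small.** This stands. The protocol gives no entry rate, and the offsets are constructed. The four patients in Section 4.4 had reinfection after liver transplantation, so they show that enzymes can fall on the drug, not how often they are raised in this population.
- **A reader might infer that the adverse-event rule has the same fault**, because Section 10.7 says "Out-of-range data judged as clinically significant (CS) by the Investigator has to be report as an adverse event" and adds no baseline condition. The documents do not support that. Section 10.1 requires a temporal association and names exacerbation of an existing condition. Section 10.2 admits an abnormal test only with symptoms, further work-up or intervention, or a change in dosing or participation. Section 10.3 leaves the classification to the investigator and recognises underlying disease as an explanation. A stable, known elevation need not become an adverse event. Restricting laboratory events to values worse than day 1 would narrow safety reporting and conflict with collection of events from consent.

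**Conclusion.** The point holds for the secondary 1x/2x laboratory summary in Section 12.1 and the synopsis. As written it counts abnormality present at entry as a safety result, in an uncontrolled trial whose population makes such abnormality plausible and whose entry criteria do not exclude it. With no drug effect the table would read 6/20 to 18/20 if 30-90% of patients were abnormal on day 1. That range is an assumption, and the true figure could be lower for tests little affected by liver disease. Masking of new worsening by improvement is possible only if the percentages are compared by visit. The conclusion does not reach the primary safety analysis or the adverse-event definitions. This is a worthwhile improvement to a descriptive table, not a flaw that undermines the trial's safety assessment.

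**What to change.** In Section 12.1 and the synopsis, keep the 1x and 2x categories but present them for each test as a by-patient shift table: category on day 1 (pre-dose) against worst category on days 2-15. Give the percentage newly crossing each limit, with exact 95% CI, among patients who were not already beyond that limit on day 1, and print that denominator. For patients already abnormal on day 1, add the change from, or the multiple of, the day-1 value, so that worsening within a category is visible. Leave the reporting rule in Section 10.7 unchanged.

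The cost is a short rewording in two places. The day-1 and later values are already scheduled, so no sample or visit is added. The drawback is precision: at-risk groups can be small. At an assumed 90% entry abnormality, only two patients could newly cross, and 0/2 has an upper limit of 84.2%. The change-from-day-1 summary is needed alongside the shift table for that reason.
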